## Abstract

**Background:**

Edgewise fixed orthodontic appliances are available in two different bracket slot sizes (0.018 and 0.022 inch). Both systems are used by clinicians worldwide with some orthodontists claiming the superiority and clinical advantages of one system over the other. However, the scientific evidence supporting this area is scarce and weak. This leaves the clinician’s choice of bracket slot system to clinical preference. We aim to compare the 0.018-inch and 0.022-inch pre-adjusted bracket slot systems in terms of the effectiveness of orthodontic treatment.

**Methods/Design:**

This is a prospective, multicenter, randomized clinical trial, undertaken in the secondary care hospital environment in the NHS Tayside region of Scotland (United Kingdom). A total of 216 orthodontic patients will be recruited in three centers in secondary care hospitals in NHS Tayside. The participants will be randomly allocated to treatment with either the 0.018-inch or 0.022-inch bracket slot systems (n = 108 for each group) using Victory series™ conventional pre-adjusted bracket systems (3 M Unitek, Monrovia, United States). Baseline records and outcome data collected during and at the end of orthodontic treatment will be assessed. The primary outcome measures will be the duration of orthodontic treatment in the maxillary and mandibular arches. The secondary outcome measures will be the number of scheduled appointments for orthodontic treatment in the maxillary and mandibular arches, treatment outcome using Peer Assessment Rating index (PAR), orthodontically induced inflammatory root resorption (as measured using periapical radiographs) and the patient’s perception of wearing orthodontic appliances.

**Discussion:**

The results from the current study will serve as evidence to guide the clinician in deciding whether the difference in bracket slot size has a significant impact on the effectiveness of orthodontic treatment.

**Trial registration:**

Registered with ClinicalTrials.gov on 5 March 2014, registration number: NCT02080338.

## Background

Malocclusion is a common worldwide dental problem, often causing aesthetic and functional concerns, which can lead to a negative impact on the quality of life [1, 2]. Malocclusion is normally corrected using orthodontic treatment which includes fixed and/or removable braces. There are a number of fixed appliance systems used in contemporary orthodontics which include multiple pre-adjusted edgewise fixed appliance systems. Edward H Angle is regarded as the father of modern orthodontics and introduced the ‘edgewise’ bracket into orthodontic treatment in 1925 as a development of the ‘ribbon arch’ appliance. The interaction between the edgewise bracket slot and the orthodontic archwire can determine the nature of the orthodontic forces. In order that the gold archwires were sufficiently rigid, Angle proposed the bracket slot dimensions be 0.022 by 0.028 inches. The advent of stainless steel alloys facilitated the use of smaller dimension wires with the same rigidity as that of the larger gold alloy archwires. This allowed the bracket slot size to be reduced, and as a result the 0.018-inch bracket slot was introduced into orthodontics. However, the introduction of the 0.018-inch bracket slot did not eliminate fixed appliance systems using 0.022-inch bracket slots from clinical practice [3].

In the last 20 years, a number of other alloy archwires have been developed. These include standard nickel titanium, thermally activated nickel titanium, superelastic nickel titanium and titanium-molybdenum archwires. Despite these advances in metallurgy, no high quality studies have sought to investigate the effectiveness of 0.018-inch compared with 0.022-inch bracket slots in orthodontic treatment. Only two retrospective studies have compared the duration of treatment for patients treated with 0.018-inch slot and 0.022-inch slot fixed appliance systems [4, 5]. It is interesting to note that these two studies reported a statistically significant reduction in the mean orthodontic treatment duration for the 0.018-inch slot system; however, this difference was not considered by the authors to be clinically significant.

A number of biomechanical advantages and disadvantages have been suggested for both 0.018-inch and 0.022-inch bracket slots. It has been postulated that overbite reduction (a key stage in fixed appliance orthodontic treatment) and closure of any residual extraction space may be more efficient with 0.022-inch bracket slots as the space between the working archwire (0.019 by 0.025-inch stainless steel) and the 0.022-inch bracket slot (known as slop) allows exaggerated bite-opening bends to be placed whilst still being able to be fitted with relative ease [6]. Conversely, the working archwire (0.016 by 0.022-inch stainless steel) for 0.018-inch bracket slots is presumed to deliver third order movement (known as torque) more effectively and earlier in treatment without additional wire bending [6].

All fixed appliance orthodontic treatment results in adverse effects on the roots of the teeth, the most common being orthodontically induced inflammatory root resorption (OIIRR). Excessive forces during treatment have been associated with iatrogenic damage including OIIRR, periodontal destruction, loss of crestal bone height and loss of pulp vitality. It is not known if these are actually significantly reduced when 0.018-inch bracket slots are used, although different appliances are associated with differing levels of biological trauma during treatment [7]. A retrospective study by Sameshima and Sinclair [8] which investigated multiple treatment factors for the prediction and prevention of OIIRR reported that difference in bracket slot size was not significantly associated with OIIRR.

The preference for each slot size varies throughout the world. In the United Kingdom, the majority of orthodontists continue to use 0.022-inch bracket slots. However, in the rest of mainland Europe, 0.018-inch bracket slots are more commonly used, whilst in the United States, the majority of orthodontists work with 0.022-inch bracket slots. It has been estimated that approximately 10% of Americans relocate to another state each year and this is likely to also be true for Europe and the United Kingdom [9]. When patients undergoing orthodontic treatment transfer to a different orthodontist, the dichotomy in orthodontic bracket sizes is not only inconvenient for the new orthodontist if appropriate inventory is not kept in stock, but unnecessary potential side-effects can occur if active treatment is prolonged. These biological and clinical management problems could all be avoided or minimized if one slot size was shown to be superior and subsequently adopted by the profession as the international standard [3, 9].

The aim of this trial is to provide reliable evidence for clinicians as to whether the use of 0.018-inch or 0.022-inch bracket slot systems has any impact on the effectiveness of orthodontic treatment. We will do this by determining if the use of 0.018-inch and 0.022-inch bracket slot systems has any effect on the duration or quality of result of orthodontic treatment, patient’s perception of treatment or the biological side effects associated with orthodontic treatment. We hypothesize that there is no difference in the outcomes of orthodontic treatment (as listed above) using either a 0.018-inch or 0.022-inch slot fixed appliance system.

## Methods/Design

### Trial design

The current trial is a multicenter, two-arm, parallel group, randomized controlled trial (Figure 1) designed following the CONSORT guidelines [10]. Patients who give informed consent to participate in this study will be entered into the study database, which will be held on one of the computers within the Orthodontic Department at Dundee Dental Hospital and School. Each participating patient will be allocated the next available study number at the start of active treatment using a series of opaque envelopes containing the treatment group.

**Figure 1 Fig1:**
[figure not shown]
**Trial CONSORT flow chart with projected numbers of participants throughout the trial.** Intervention 1: 0.018-inch bracket slot system and intervention 2: 0.022-inch bracket slot system.

This trial will recruit orthodontic patients from three sites in secondary care setting in NHS Tayside, Scotland: Dundee Dental Hospital and School, Perth Royal Infirmary and Springfield Medical Centre (Arbroath). Prior to study recruitment at any individual site, there will be a site initiation visit and site staff will receive training on the study design, methodology, clinical intervention and maintaining trial documentation, including the case report forms questionnaires and investigator site file.

### Participant inclusion criteria

Patients scheduled to undergo dual arch fixed appliance orthodontic treatment in any of the three trial centers will be invited to participate in this trial by the operator planning to conduct their orthodontic treatment. Patients who are eligible to receive treatment in the NHS Scotland should have a significant need of treatment which requires an Index of Orthodontic Treatment Need (IOTN) score of 4 or 5 for the dental health component, or a score of 3 combined with a high aesthetic component score (>5) [11]. All types of malocclusions (Class I, II and III malocclusions) will be recruited to the study including cases which require extraction or non-extraction as part of the treatment plan.

### Participant exclusion criteria

Participants will be excluded if they fulfil any of the following criteria: patients who have undergone previous orthodontic treatment including fixed, removable and functional appliances; patients less than 12-years-old at the start of orthodontic treatment; patients with orofacial clefting, severe hypodontia and special needs patients; and patients undergoing orthognathic (jaw) surgery as part of their orthodontic treatment plan.

### Intervention protocol

All teeth will undergo pumice and water prophylaxis immediately before bonding and banding. The teeth will then be prepared using self-etching primer (Transbond™ Plus Self Etching Primer, 3 M Unitek, Monrovia, United States). Depending on the card inside the participant’s envelope, either 0.018-inch or 0.022-inch slot Victory Series™ McLaughlin, Bennett, Terevisi (MBT) prescription adhesive pre-coated (APC) brackets and buccal tubes (or bands, where appropriate) (APC™ II Victory Series Twin MBT™, 3 M Unitek, Monrovia, United States] will be placed. A standardized wire sequence for each bracket slot system will be followed whenever clinically appropriate. The 0.018-inch bracket slot system archwire sequence will be: 0.016-inch nickel titanium alloy archwire, followed by 0.016 × 0.022-inch nickel titanium alloy archwire followed by 0.016 × 0.022-inch stainless steel archwire. The 0.022-inch bracket slot system sequence will be: 0.016-inch nickel titanium alloy archwire, followed by 0.019 × 0.025-nickel titanium alloy archwire followed by 0.019 × 0.025-inch stainless steel archwire.

A flow chart for the study (Figure 2) showing the key steps will be attached to the participant’s clinical case notes to help remind clinicians to adhere to study protocol. A standardized clinical treatment regime will be used throughout the trial, accepting that clinical circumstances may necessitate deviations from the standard protocol.

**Figure 2 Fig2:**
[figure not shown]
**Trial key steps diagram.** Showing the pre-treatment, mid-treatment and end of treatment records collected. Smile better questionnaire is completed by the study participants with regards to their experience wearing the fixed appliances. Index of Orthodontic Treatment Need Aesthetic Component (IOTN AC), Orthopantomograph (OPT).

### Outcome measures

At the end of the trial, the standardized records will be anonymized before any scoring will be undertaken. Thus the investigator will be blind to the allocation before any observations are recorded in order to eliminate investigator bias.

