### Blinding

Due to the nature of the trial it is not possible to blind the clinician to the group once it is allocated. Once the opaque numbered envelope used for random allocation is opened and the clinician and participant know which appliance type (either 0.018-inch slot or 0.022-inch slot) will be used, the appliance will be clearly specified on the pro forma kept within the patient’s case notes. This will allow the clinician to adhere to the recommended standard archwire sequence for each type of appliance.

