### Data and records to be collected

The following standardized data will be recorded for the trial participants at three stages of orthodontic treatment. Before start of orthodontic treatment: full orthodontic diagnostic clinical assessment, orthodontically trimmed study models at the start of orthodontic treatment, IOTN (aesthetic component score), long-cone paralleling technique periapical radiographs of maxillary central incisors, lateral cephalometric radiographs recorded before the start of treatment and patient questionnaire (pre-treatment). During orthodontic treatment: treatment duration, number of appointments, dates of key stages in fixed appliance orthodontic treatment, number of fixed appliance components replaced during active treatment, patient questionnaires (Smiles Better) regarding their perception of the impact of treatment (completed by the patient at six months from the start of orthodontic treatment), long-cone paralleling technique periapical radiographs of maxillary incisors recorded at nine months after the start of orthodontic treatment using digital radiography and lateral cephalometric radiograph recorded before the completion of active treatment.

End of orthodontic treatment: orthodontically trimmed study models at the end of treatment, patient questionnaire (post-treatment) and IOTN (aesthetic component score).

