### Data management

A data collection sheet designed specifically for the current trial will be used to collect data from all participants’ records including study models, patient questionnaires, case notes and radiographs. The data collection sheet will be coded to allow for the blinding of the investigator to the type of appliance used during data analysis. The data will then be uploaded into a validated excel sheet specially designed for the current trial complying with Good Clinical Practice regulations. At the end of the trial the data will be exported into SPSS (Statistical Package for Social Sciences, Inc., Chicago, Illinois, United States) v.18 for statistical analysis.

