### Emergency code-breaking procedure

Emergency code-breaking in this randomized control trial is not applicable because the bracket slot size system used for each participant will be clearly detailed within the patient’s clinical notes. The proposed intervention is unlikely to result in significant adverse events. However, should they occur, they will be recorded in keeping with routine clinical practice.

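### Anonymising the records does not by itself secure blinded scoring, because the data sheet is also filled from case notes that name the slot size

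*Protocol article*

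**What the plan says.** All references are to the protocol article.

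- **Outcome measures** gives the step taken: "At the end of the trial, the standardized records will be anonymized before any scoring will be undertaken". The next sentence presents blinding as its consequence: "Thus the investigator will be blind to the allocation before any observations are recorded in order to eliminate investigator bias".
- **Data management** describes one data collection sheet, completed from participants' "records including study models, patient questionnaires, case notes and radiographs". It adds: "The data collection sheet will be coded to allow for the blinding of the investigator to the type of appliance used during data analysis".
- **Blinding** says that, once the envelope is opened, the appliance "will be clearly specified on the pro forma kept within the patient’s case notes".
- **Emergency code-breaking procedure** treats code-breaking as not applicable because "the bracket slot size system used for each participant will be clearly detailed within" the clinical notes.
- **Secondary outcomes** takes OIIRR from periapical films at nine months of active treatment, incisor torque from a cephalogram late in treatment, and PAR from study models at start and end. **Data and records to be collected** confirms the timing of the second film: "lateral cephalometric radiograph recorded before the completion of active treatment".

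**The concern.** Clinician and participant both know the allocation, so blinded scoring is the main protection left for outcomes that need a reader's judgement. The article claims that protection in strong terms: blindness before anything is recorded, and investigator bias eliminated. The mechanism it offers is anonymising, which hides identity rather than treatment. Documents that state the treatment openly are also listed as a source for the sheet on which the outcomes are recorded.

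Two comparisons are at stake in particular. OIIRR is the biological harm outcome, and its grading depends on how the reader sees the root apex. Incisor torque tests an advantage that the Background attributes to the 0.018-inch system, and the angle depends on where the reader draws the tooth axis. A reader who knows the arm could shift either without intending to.

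**Working it through.** The plan gives no figure for blinding, so there is none to reproduce. The check sets the sections side by side and adds one small calculation on what a film could show.

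**Step 1: does the stated mechanism give the stated result?**

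| Question | What the article provides |
|---|---|
| What is removed before scoring? | Identity (Outcome measures) |
| What must be hidden for blinding? | Slot size |
| Where is slot size written? | In the notes (Blinding; Emergency code-breaking procedure) |
| Do the notes feed the data sheet? | Yes (Data management) |
| Is slot size masked in the notes? | Not stated |
| What does the coding cover? | The sheet, for data analysis (Data management) |
| Are note extraction and scoring done by different people, or in a fixed order? | Not stated |

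The coding acts on the sheet, not on the source records. Someone with the notes open can see the slot size while filling in a coded sheet. The coding therefore protects analysis, whereas Outcome measures claims protection before observations are recorded.

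**Step 2: which outcomes are exposed?**

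- OIIRR and incisor torque are reader-judged from films. They are exposed through the notes and possibly through the films.
- PAR is reader-judged from models. It is exposed through the notes only.
- Treatment duration, number of visits and components replaced are recorded during treatment, and case notes are their natural source. They are counted rather than graded, but whoever extracts them from notes that name the slot is not blind.
- The aesthetic component rating and the questionnaires come from the participant, who knows the allocation. Blinding the scorer does little for these.

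**Step 3: could the films reveal the arm?** Both films are taken during active treatment, so the appliance is normally in place. Dimensions are from Intervention protocol; millimetres = inches × 25.4.

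- Slot: 0.022 − 0.018 = 0.004 inch; 0.004 × 25.4 = 0.10 mm.
- Final wire, smaller dimension: 0.019 − 0.016 = 0.003 inch; 0.003 × 25.4 = 0.08 mm.
- Final wire, larger dimension: 0.025 − 0.022 = 0.003 inch; 0.003 × 25.4 = 0.08 mm.

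Both arms use the same bracket family and prescription, and both wire sequences start with a 0.016-inch nickel titanium wire. The article does not say which wire is in place at nine months, and gives no image resolution. Whether a reader could see differences of this size is not settled by the document.

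**The case against.** The strongest reply is that the article condenses a fuller protocol. Who extracts notes, who scores and in what order are operational details that an article commonly omits. Data management lists sources; it does not say that one person handles all of them. Taken with the anonymising and the coding, the text shows a clear intent to hide the arm.

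Much of this stands. Silence about staffing alone would be no finding, and the intent is plain. What remains is that the article does not merely leave the mechanism out. It states one, and draws from it a conclusion that the mechanism cannot support, while its own sections on data sources and case notes leave an open route to the allocation.

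A reader might infer three stronger things that the document does not support:

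- **That the scorer is in fact unblinded.** No section says that the scorer sees the notes. The fault is that nothing prevents it.
- **That the films give the arm away because the appliance is visible.** With one bracket family and differences of 0.08 to 0.10 mm, visibility of the appliance is not recognition of the arm.
- **That all 216 participants are affected.** The notes of every treated participant should name the slot, but that counts notes, not scorings made with knowledge of them.

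It is also fair to object that masking images is not free of risk. The bracket sits on the incisor crown, and the axis has to be drawn through that tooth. Masking is therefore a conditional extra and not the core of the remedy.

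**Conclusion.** The concern holds in a limited form: blinding of scoring is asserted, but anonymising alone does not secure it. The case-note route rests directly on the text. The film route is a possibility that depends on image quality and on the wire in place, neither of which is given.

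The exposure is greatest for two film-based secondary measures (OIIRR and incisor torque) and extends to PAR only through the notes. Duration, the primary outcome, is not graded by a reader, so this point does not threaten it in the same way. The direction and size of any observer bias cannot be derived from the document.

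The conclusion assumes that no unshown procedure already separates or orders extraction and scoring. If one exists, the remedy reduces to stating it. This is an inexpensive improvement to make before records are scored, not a defect that invalidates the trial.

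**What to change.** Amend Outcome measures and Data management as follows:

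1. Score study models and radiographs first, under a random code that carries no information on the arm, and lock those scores.
2. Open the case notes only after that, to extract duration, visits and replaced components.
3. Crop or mask the bracket and wire areas on the images only where the root apex and the landmarks for the incisor axis remain measurable. Where they do not, leave the image as it is and say so.
4. Limit the blinding claim to the outcomes scored this way, and state that items taken from notes naming the slot are not blinded. Drop the claim that investigator bias is eliminated.

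The cost is an agreed order of work and some preparation time per image where masking is used. It needs no further patient visit, no extra radiograph and no change to treatment.

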#### Primary outcome

The primary outcome will be the duration of orthodontic treatment (measured in months) required to finish orthodontic treatment in both the maxillary and mandibular arches, including the number of visits required to complete treatment.

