#### Statistical analysis

Table 1 shows the planned statistical tests to be used for each variable investigated. The significance level will be set to α = 0.05 (two-tailed).

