**Table 1 Tab1:** **Statistical tests**

Outcome measure		Type of variable	Statistical test ***P***<0.05
**Primary outcome**	Duration of alignment stage for the upper and lower arches	Continuous, assuming normal distribution	One-way ANOVA test
**Secondary outcomes**	Number of visits required	Continuous, assuming normal distribution	One-way ANOVA test
	Occlusal outcome PAR	Continuous, assuming normal distribution	One-way ANOVA test
	Patient perception	Categorical data	Chi-square test
	Severity of OIIRR	Categorical data	Chi-square test or Friedman test

A list of statistical tests that will be used for data analysis depending on the type of data in the current trial. Peer Assessment Rating index (PAR), orthodontically induced inflammatory root resorption (OIIRR), analysis of variance (ANOVA).

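### The primary outcome is stated inconsistently: visits are both primary and secondary, one or two arch durations are possible, and Table 1 names a different treatment stage

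*Protocol article*

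**What the plan says.** The protocol article describes the primary outcome in four places, and they differ.

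- **Primary outcome section:** a duration in months, "required to finish orthodontic treatment in both the maxillary and mandibular arches", with the addition "including the number of visits required to complete treatment".
- **Abstract, Methods/Design:** "The primary outcome measures will be the duration of orthodontic treatment in the maxillary and mandibular arches". Visits are placed elsewhere: "The secondary outcome measures will be the number of scheduled appointments for orthodontic treatment in the maxillary and mandibular arches".
- **Target sample size:** refers to treatment duration as a single primary outcome and sizes the trial for one difference in means.
- **Table 1:** has one primary row, "Duration of alignment stage for the upper and lower arches", with a one-way ANOVA. "Number of visits required" stands under the secondary outcomes.

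The Secondary outcomes section numbers three secondary outcomes, and visits are in none of them. The Statistical analysis section sets one two-tailed level of 0.05 for the tests in Table 1.

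**The concern.** A primary outcome should be one variable, identifiable from any part of the plan. Here three features are unsettled: whether visits belong to it, whether the two arches give one duration or two, and whether the clock covers the whole treatment or only alignment.

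Months and a count of visits cannot be one variable unless a composite is defined, and none is. A one-way ANOVA takes one response per patient. If each arch has its own duration, the test must either be run twice or be fed two correlated values from the same patient.

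The risk is that the deciding variable gets chosen after the data are seen. A reader of the results could then not tell whether a significant finding in one arch, in visits or in the alignment stage was the planned primary result.

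**Working it through.** **1. The descriptions side by side**

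| Place | Visits | Arches | Stage |
|---|---|---|---|
| Abstract | secondary | plural measures, by arch | whole treatment |
| Primary outcome | inside the primary | one duration, both arches finished (most natural reading) | whole treatment |
| Secondary outcomes | not listed | – | – |
| Target sample size | not mentioned | one duration | whole treatment |
| Table 1 | secondary | one row naming both arches | alignment stage |

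The status of visits is a direct contradiction: the Methods text puts them only in the primary, while the Abstract and Table 1 put them only in the secondary outcomes. The stage is also a direct contradiction, between Table 1 and the rest. The number of arch durations is an ambiguity.

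**2. The plan's own sample size**

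Inputs from Target sample size: difference 3 months, SD 7.2, two-sided 0.05, power 80%.

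- Normal approximation: n = 2 × (7.2/3)² × (1.960 + 0.842)² = 90.4, so 91 per group.
- Exact t-test: the noncentrality at n = 92 is 3 / (7.2 × √(2/92)) = 2.826, with 182 degrees of freedom. Power is 80.3% at 92 and 79.8% at 91.

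The stated 92 per group is reproduced for one duration endpoint.

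**3. False-positive rate if any significant primary test counted as success**

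This rule is an assumption; the article does not state it. For k independent tests at 0.05 the rate is 1 − 0.95^k: 1 − 0.95² = 9.75% for two and 1 − 0.95³ = 14.3% for three. For correlated tests it is 1 − P(all |Z| < 1.960), with Z equicorrelated normal, by numerical integration. The correlation is not in the article, so a range is shown.

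| Correlation (assumed) | Two arches | Two arches plus visits |
|---|---|---|
| 0 | 9.8% | 14.3% |
| 0.5 | 9.1% | 12.5% |
| 0.7 | 8.3% | 10.9% |
| 0.8 | 7.8% | 9.8% |
| 0.9 | 7.0% | 8.4% |
| 0.95 | 6.5% | 7.3% |

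Both arches belong to the same patient and the same course of treatment, so a high correlation is more plausible than none. The lower rows are then the relevant ones.

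**4. What keeping both arches primary would cost**

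This assumes the same 3 months and SD 7.2 in each arch.

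- Either arch sufficient, with 0.025 for each: 111 per group are needed for 80% power per test. At 15% to 20% dropout that means recruiting 222/0.85 = 262 to 222/0.80 = 278, against the planned 216. With 92 per group the power per test is 71.4%.
- Both arches required at 0.05: the error rate is not inflated, but power at 92 per group is 65% to 77% for correlations from 0 to 0.95.

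Only the single-duration reading fits the planned numbers.

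**The case against.** The strongest reply is that the article, read as a whole, means one duration. The Primary outcome section uses the singular and most naturally describes the time until both arches are finished. The sample size section is singular too, and Table 1 has one primary row with one test. Only the Abstract's plural clearly points to two measures.

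Much of this stands. A reader might infer that the arches are separate primary outcomes, each tested at 0.05, so that the trial's 5% error rate is lost. The article does not say so. It gives a general level for the tests in Table 1, assigns none to each arch, and states no rule under which either arch would suffice. A reader might also infer that the sample size is wrong, but it is right for one duration endpoint and falls short only under rules that the article does not state.

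A second reply is that multiplicity handling is commonly left to a fuller protocol or analysis plan. That is fair, and the absence of a multiplicity rule is not the point here.

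Neither reply removes what is on the page. Visits are primary in one section and secondary in two other places, and the stage in Table 1 disagrees with the definition and with the sample size. The article's own statistical analysis section does not resolve either conflict.

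**Conclusion.** Wrong as written. The contradictions over visits and over the treatment stage are certain from the text; the question of one or two arch durations is a real ambiguity. The effect on the error rate is conditional. It arises only if any one of several primary tests may carry the trial, and is then about 6.5% to 9.8% for two arches and 7.3% to 14.3% with visits added, over assumed correlations of 0.95 to 0. With a single overall duration, or if both arches had to be significant, it does not arise. The planned 92 per group stands for one duration endpoint.

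**What to change.** Before any outcome analysis, by dated amendment:

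1. Name one primary variable: total treatment duration in months per patient, until both arches are finished, with one two-sided test at 0.05.
2. Delete "including the number of visits required to complete treatment" from the Primary outcome section.
3. List visits and arch-specific durations as secondary, in the Secondary outcomes section as well as in the Abstract and Table 1.
4. In the Abstract, replace the plural arch-specific primary measures with the single variable.
5. In the Table 1 primary row, replace the alignment stage with whole-treatment duration.

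The cost is wording only. No patients are added and no power is lost, because the sample size already assumes one duration. What is given up is primary status for arch-specific results. If both arches are to stay primary, the alternative is to state the decision rule and size the trial for it, at the cost shown in the working.
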